### **The Study Population**

[figure not shown]

The alarming prevalence rates of diabetes and diabetes-related complications and their profound and disparate consequences in African-American and Hispanic women are a subject of universal concern. Collectively, our four study centers have access to a unique distribution of women with high risks of diabetes and The Metabolic Syndrome: The University of Tennessee serves a large community of African-American and Vietnamese women; the Albert Einstein Centers, with affiliated practices located in the Bronx and the Washington Heights section of Manhattan, provide an opportunity to enroll women of several Latina heritages; and The New York Medical College - Westchester Medical Center site currently follows a large, socio-economically diverse, South Asian population that includes many staff health care professionals and their families, as well as Asian-Americans from neighboring communities. Clearly, minority women from all these communities are a critical target for early preventive interventions.

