| 
Study Design
          | 
Overview
<small>Please see attached Study Flow Chart</small>
 
Chart review of patients at the 3 study Centers and their affiliated General Medical and Gynecology practices and public announcements will be used to identify non-diabetic women who meet selection criteria who will be invited to participate in the study. After obtaining consent, and additional screening for suitability, 80 patients will undergo glucose tolerance testing and additional tests to determine if they meet study inclusion and exclusion criteria. Following a 1-month lead-in phase, an initial study population of 75 women from 3 clinical sites will be randomized to placebo (diet and lifestyle modification) or one of two active study treatment arms for a 6-month study (Phase 1); patients in the diet plus placebo group will then be crossed over to one of the two active study arms for a 2nd six months (Phase 2).
 |
| 
Inclusion / Exclusion
 | 
Inclusion Criteria
 
 
1. Healthy, non-diabetic women with "≥20 pound weight gain since their twenties"
 
2. Age: 35-55
 
3. Peri-menopausal ( FSH ≥25 on day 2-3 of cycle) or postmenopausal status
 
4. Body Mass Index (BMI) 25-35 kg/m^2
 
5. Either:             
 
(a). a single blood pressure recording ≥135/85 or the use of blood pressure medication
 
OR
 
(b) HDL≤50mg/dl or triglycerides ≥150 mg/dl or the use of lipid modifying medication
 
 
 
7. Area-under-the-curve (AUC-)insulin level ≥100μU/ml along with normal fasting (≤100 mg/dl) & postprandial (≤200 mg/dl) glucose determinations following a 75-gram standard oral glucose tolerance test.
 
 
Exclusion Criteria
                                                             |

[figure not shown]

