|--------------------------------------------------------------------------------------------------------|--------------------------------------------------------------------------------------------------------------------------------------------------------------------------------------------------------------------------------------------------------------------------------------------------------------------------------------------------------------------------------------------------------------------------------------------------------------------------------------------------------------------------------------------------------------------------------------------------------------------------------------------------------------------------------------|
| Number of Patients                                                                                     | Total enrollment 75-85 (approx. 20 per site) to capture 60 patients completing the study                                                                                                                                                                                                                                                                                                                                                                                                                                                                                                                                                                                             |
| Projected Enrollment Timeline (proposed start date, proposed finish date, anticipated enrollment rate) | 
Please see attached timeline
 
Projected start date: Sept 1, 2006
 
Projected study completion date: August 30, 2008 (without optional phase)
 
Time-table assumptions:
 
The investigators anticipate a rapid study start-up phase due to:
 
 
a. general ease of enrollment of obesity studies
 
b. investigators' access to large and diverse patient populations in their individual practices and the community
 
c. availability of field tested patient education materials and study instruments
 
d. the availability of nursing and nutrition staff with broad
 
 |

[figure not shown]

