|                                                   | 
experience in the conduct of clinical trials (e.g., The Women's Health Initiative, Diabetes Prevention Trial) in related areas.
 
These factors will improve the study efficiency and reduce study costs.
                                                                                                                                                                                                                                                                                                                                                                                                                                                                                                                                                                                                                                                                                                                                                                                                                                 |
| Drug Dose
(doses, dosing, frequency, duration) | 
The three arms will use:
 
 
1. placebo Avandamet® (using the dosage schedule for placebo metformin in the metformin arms below).
 
2. Metformin, initial dose 500 mg BID with titration to 2000mg/day (by adding one 500mg tab weekly on weeks 3 and 4).
 
3. Avandamet 2 mg BID plus metformin 500 mg BID (to be titrated to 2000 mg/day.)
 
 
The study can also be done with a dual placebo regimen, i.e., substitution of a placebo tablet for both metformin and rosiglitazone, such that placebo and metformin arms receive placebo RSG and the Avandamet arm receives separate tabs for MF and RSG. A detailed table with an initial weekly dosage schedule for all medications in the 3 arms for the lead-in and subsequent phases can be provided on request.
 
The Study Pharmacist at Westchester Medical Center who oversees randomization in several hundred clinical trials per year will perform the randomization and distribute medication to all sites.
 |

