#### Statistical Plan

Mean, median, range and distribution of all baseline study variables will be determined (SPSS (13.0); site differences will be assessed using an Analysis of Variance (ANOVA). All primary and secondary outcome variables will be evaluated using an intention-to-treat analysis with a last observation carried forward (LOCF) for missing data, Paired t-tests will be used to calculate baseline changes in insulin parameters, body weight, BMI, cardiovascular risk factors, and related serum markers (adiponectin, leptin, ghrelin, resistin, C-reactive protein and other inflammatory markers, vitamin D and IGF-binding proteins at 6 and 12 months. Non-parametric measures will be used for comparison of group mean changes at 6 and 12 months. Statistical models will be used to calculate the primary (crude, non-adjusted) treatment effect of the respective study arms and for covariate adjustment by age, initial BMI category and menopausal status,

[figure not shown]

|  |                 |
|--|-----------------|
|  | and study site. |
|--|-----------------|

Publication / Presentation Plan:

Following the analysis of baseline data, abstracts will be submitted for presentation at annual meetings, including The Endocrine Society, The ADA, The American College of Cardiology, NAASO (The National Association for The Advancement of the Study of Obesity, NAMS, (The North American Society for Menopause). Publications will be prepared and submitted at regular intervals, following the collation of baseline data, and the completion of each study phase. A final summary manuscript will be submitted within 6 months of the study completion.

Estimated Study Budget/Requested Support (per patient cost, study medication, other supplies):

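### The primary treatment effect is crude and leaves study site out, which gives up power if sites differ on the outcome; site belongs in the primary model

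*Protocol*

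**What the plan says.** - **Primary effect.** The Statistical Plan gives as primary the "crude, non-adjusted) treatment effect of the respective study arms". The same sentence goes on to a covariate adjustment by age, BMI category, menopausal status and study site. Site differences in baseline variables are to be assessed by ANOVA, and group mean changes compared by non-parametric methods.
- **Sample size.** The Summary of sample size calculations uses an analysis of covariance: 60 patients, 20 per group, f = 0.38, two-sided 0.05, at least 80% power, raised to 25 per group for 20% attrition.
- **Site populations.** Under The Study Population, Tennessee "serves a large community of African-American and Vietnamese women", the Einstein centers "provide an opportunity to enroll women of several Latina heritages", and the Westchester site follows a largely South Asian population.
- **Allocation.** The Drug Dose row says the Westchester study pharmacist "will perform the randomization and distribute medication to all sites". It gives no list type, block size or stratum.
- **Number of sites.** The Study Design overview says "an initial study population of 75 women from 3 clinical sites will be randomized". The Study Population says "our four study centers have access to a unique distribution of women". The Number of Patients row says "Total enrollment 75-85 (approx. 20 per site) to capture 60 patients completing the study".

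**The concern.** The protocol treats site as important enough to test at baseline and to adjust for, but the effect it labels primary does not use it. If women at different centers respond differently on average, whatever their treatment, that variation stays in the residual of the primary comparison and widens its standard error. In a trial planned around 60 completers there is little power to spare. Site is known at entry and its adjustment is already planned, so leaving it out of the primary model saves nothing. Allocation bears on this because, unless lists are kept by site, arms will often be uneven within a site, and a crude comparison cannot correct for that.

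**Working it through.** **Inputs from the protocol.** N = 60 completers, 3 groups, f = 0.38, alpha 0.05, 75 randomised.

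**Assumed.** The share r of outcome variance explained by site, because the protocol gives no figure. With three equal sites and within-site SD 1:
- means at -0.25, 0, 0.25: between-site variance = 2 × 0.0625 / 3 = 0.0417, so r = 0.0417 / 1.0417 = 4%;
- means at -0.5, 0, 0.5: between-site variance = 2 × 0.25 / 3 = 0.1667, so r = 0.1667 / 1.1667 = 14%.

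**1. The plan's own figures.** 60 / (1 - 0.20) = 75 reproduces. For the 2-df F test, lambda = N f² = 60 × 0.1444 = 8.664. With 57 denominator df, power is 73.0%, not 80%. The stated 80% is reached only under readings the protocol does not give, such as a baseline covariate correlated about 0.385 with the outcome, or a 1-df contrast. That is a separate matter; 73% is the reference here.

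**2. Crude against site-adjusted power.** Take f = 0.38 on the within-site SD. The crude analysis then has effective f = 0.38 × sqrt(1 - r), so lambda = 8.664 × (1 - r), with 57 df. The site model keeps lambda = 8.664 with 55 df (three sites) or 54 df (four).

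| Site share r (assumed) | lambda, crude | Power, crude | Power, site in model |
|---|---|---|---|
| 0% | 8.664 | 73.0% | 72.9% |
| 4% | 8.317 | 71% | 73% |
| 10% | 7.798 | 68% | 73% |
| 14% | 7.451 | 66% | 73% |

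With four sites the last column is 72.8%. If f = 0.38 is instead meant on the total SD, crude power stays at 73% and the site model gains: at r = 14%, f becomes 0.38 / sqrt(0.86) = 0.410, just short of the 0.412 or so needed for 80%.

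**3. False-positive rate.** Simulation with 60 patients at three sites of 20, a list balanced overall but not by site, and r from 0 to 20%: the crude test rejects a true null in 4.9% to 5.4% of trials. That is nominal.

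**4. Does stratifying alone help?** At r = 20%, simulated power of the crude test is 61% whether or not allocation is stratified by site (blocks of 6). With stratification its type I error falls to 2.6%, so the test is conservative. With site in the model and stratified allocation, power is 73% and type I error 5.0%. The model term does the work.

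**5. How uneven could sites be?** For 25/25/25 allocated over three sites of 25 without strata, every possible set of site-by-arm counts can be weighted by its multinomial coefficients. The chance that some site has one arm at least twice another is 51%, and the chance of a gap of 6 or more between arms at some site is 47%. With site-stratified blocks of 6, no simulated allocation had a gap that large.

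**The case against.** The strongest reply is that site adjustment is already planned in the same sentence, so the dispute is only about which of two estimates leads. It adds that the word primary there may mean no more than the first, unadjusted step. This is fair and limits the size of the point. But as written, the crude effect carries the label, and the sample size was not built on a crude comparison.

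A second reply is that the assumed site shares may be too high. The outcome is change from baseline, so stable site differences in level cancel, and nothing in the protocol shows that change differs by site. That stands, and is why the result is a range that includes zero. At zero the site term costs about 0.1 point.

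Third, chance imbalance distorts little. With 25 per arm, the SD of the site contribution to an arm difference is the site SD × sqrt(2/25): 0.204 × 0.283 = 0.06 SD for the smaller spacing and 0.408 × 0.283 = 0.12 SD for the larger. The planned effect with equally spaced means puts the extreme arms 0.38 × sqrt(6) = 0.93 SD apart. The crude standard error already reflects this variation. This stands too: the within-site gaps describe the allocation and are not a measure of error in the treatment effect.

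A reader might also infer two stronger things that the protocol does not support:
- **That the allocation list is unstratified.** The Drug Dose row says who randomises, not how, and one pharmacist can hold a list per site.
- **That site and ethnicity are nearly one variable.** The Study Population describes access to communities, with more than one group at some centers, and the power assumptions leave the ethnic mix open and allow for white participants.

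**Conclusion.** The point holds as a matter of precision. The protocol fixes a crude primary effect although site is recorded, its adjustment is planned and the sample size assumes an analysis of covariance. The loss is about 2, 5 or 7 percentage points of power if site explains 4%, 10% or 14% of the outcome variance, and nothing if site explains none. This rests on the assumed shares, on f = 0.38 relative to the within-site SD, and on 60 analysed women; a larger intention-to-treat set would raise both power columns.

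It is not a validity problem. A reader might infer that the crude analysis inflates the false-positive rate or confounds drug with site. Randomisation keeps the crude estimate unbiased, and the simulated type I error is nominal. Nor would stratified allocation alone be a remedy, since with a crude analysis it recovers no power.

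**What to change.** 1. In the Statistical Plan, make the analysis of covariance with study site as a factor the model that gives the primary treatment effect, and report the crude effect as supportive. State what role the non-parametric group comparison then has, because it cannot simply take a site term.
2. Reconcile the number of sites first. The Objective and Overview and the Study Design overview give three, and The Study Population gives four centers. About 20 per site for 75 to 85 women implies 75/20 = 3.75 to 85/20 = 4.25 sites, whereas three sites would need 75/3 = 25 each. The Objective and Overview lists two Einstein units under one of the three medical centers, which may explain the difference, but the protocol does not say which unit counts as a site.
3. In the Drug Dose row, state the allocation method. If it is not already stratified, use permuted blocks stratified by site at the same central pharmacy, together with the site term in step 1.

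The cost is 2 degrees of freedom with three sites or 3 with four, and a separate allocation list for each site. No new data are needed.

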| Study Endpoints/
Objectives                    | 
The study objective is to compare the effects of metformin, and Avandamet® on markers of insulin resistance – fasting, peak (1-hour) and AUC-insulin, and HOMA-R, and body fat distribution in hyperinsulinemic, peri- and post-menopausal women with progressive weight gain (Syndrome W) prior to the onset of overt glycemic abnormalities or full-blown Metabolic Syndrome.
 
The primary outcome variables will be 1-year change in fasting and 1-hour insulin (as noted below.)
                                                                                                                                                                                                                                                                                                                                                                                                                                                                                                                                              |

|                                                                                |                                                                                                                                                                                                                                                                                                                                                                                                                                                       |
|--------------------------------------------------------------------------------|-------------------------------------------------------------------------------------------------------------------------------------------------------------------------------------------------------------------------------------------------------------------------------------------------------------------------------------------------------------------------------------------------------------------------------------------------------|

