| Outcome Parameters / Analytical Endpoints | 
The primary outcome variables are change from baseline in fasting and one-hour insulin at 1 year. Secondary outcome measures are 6 and 12 month change from baseline in body weight, CT scan-determined visceral adipose tissue other fat compartments, and relevant ratio's; total and multimeric adiponectin; and other cardiovascular risk and inflammatory markers, including lipids, c-reactive protein, TNF-<math>\alpha</math>, leptin, ghrelin, and resistin; and IGF-1 and IGF-binding proteins.
                                                                                                                                                                                                                                                                                                                                                                                                                                                                                                                                                                                                                        |
| Statistical Analysis Plan                 | 
Power Calculations and Assumptions
 
Three power calculations were performed incorporating the significance levels and sample size of TZD-based interventions in recently reported studies and comparator trials. A initial sample size of 25 per group is a realistic estimate and is based on the following assumptions:
 
 
1. Placebo treatment even with intensive dietary intervention (which will not be provided after the lead-in phase of EMPOWIR) has low rates of weight loss and high drop out rates at 6 and 12 months of study follow-up in the majority of published studies
 
2. data from observational and population based studies show annual weight gain in women in the study age range and BMI category
 
3. Metformin has a large treatment effect in hyperinsulinemic women and, in combination with hypocaloric carbohydrate modified diet, reduced fasting insulin by 25-40% and 1-hour (peak) insulin by 50% in our preliminary data. (with a mean body weight change 12.5% at 1-year).
 
4. Enrollment goals assume 10% drop out during Phase 2
 
 |

[figure not shown]

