#### Summary of sample size calculations:

The study design comprises 3 groups in one pre-treatment (Phase 1) and one post-treatment (Phase 3) measurement of outcome. Preliminary data from our open label use of metformin and other randomized clinical trials suggest that metformin affords large treatment effects. Nonetheless, as the large effect may be due in part to placebo, we will structure our sample size to detect more moderate treatment effects. Using an analysis of covariance, a sample size of 60 patients (20 per group) will provide at least 80% power to detect a moderate to large effect size ( $f=.38$ ) for a two-sided test of significance at a critical value of .05. While 20 patients per group are required to meet the anticipated effects, we will target 25 per group to allow for 20% attrition. The proposed attrition rate is less than rates reported in research studies of other medications evaluated for weight reduction, such as sibutramine (32%) and xenical (24%). However, the rate reflects attrition rates from our own preliminary data and from other published studies of patients treated with metformin analyzed using an intention-to-treat or comparable analysis such as studies of obesity in women, and children, PCOS, and HIV-related lipodystrophy.

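### Two primary insulin outcomes in three arms share one undivided .05 with no success rule, so the family-wise error rate is not fixed at 5%

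*Protocol*

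**What the plan says.** The Study Endpoints/Objectives row of the protocol states that the primary outcome variables "will be 1-year change in fasting and 1-hour insulin (as noted below". The Outcome Parameters / Analytical Endpoints row repeats them as "change from baseline in fasting and one-hour insulin at 1 year". Both rows join the two outcomes with a plain conjunction and give no success rule.

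The Summary of sample size calculations describes the design: "The study design comprises 3 groups in one pre-treatment (Phase 1) and one post-treatment (Phase 3) measurement of outcome". It sizes the trial by covariance analysis: "a sample size of 60 patients (20 per group) will provide at least 80% power to detect a moderate to large effect size", with f = .38, "for a two-sided test of significance at a critical value of .05". The effect size is not tied to either outcome, and the .05 is not divided.

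The Statistical Plan names paired t-tests for change within arms and non-parametric comparison of the groups at 6 and 12 months. It does not say whether the group comparison is overall or pairwise, and it mentions no adjustment.

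The Objective and Overview section calls the trial a pilot. It also says that placebo patients move to one of the two active arms after 6 months.

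**The concern.** Two outcomes both carry primary status, and three arms allow three pairwise contrasts per outcome. The text supplies one .05 and one calculation for a single test. After unblinding, success could be defined as fasting insulin, 1-hour insulin, either or both, and on an overall test or on any chosen pair of arms. These definitions have different false-positive rates. A reader who sees a primary result reported at .05 could not tell whether the 5% level applied to the claim being made.

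**Working it through.** **Inputs.** From the protocol: two primary outcomes; three groups; 20 completers per group; f = .38; two-sided .05; 20% attrition. Not in the protocol, and so assumed: a correlation of 0 to 0.9 between the two outcomes, and normally distributed outcomes.

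**1. The protocol's own figures.**
- Attrition: 20/(1 − 0.20) = 25 per group, 75 in total. This reproduces the target.
- Power of an overall three-group test: noncentrality f²N = 0.38² × 60 = 0.1444 × 60 = 8.664. With 2 and 56 degrees of freedom (one covariate) and no gain from the covariate, power is 73%.
- The stated figure of at least 80% is reached with a single-degree-of-freedom contrast (82.5%), or if the covariate correlates at about 0.385 with the outcome: 8.664/(1 − 0.385²) ≈ 10.17, power 80%. The protocol states neither, so its power figure is not shown to be wrong. It does show that the deciding test is not identified.

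**2. Error rate under each possible success rule.** For two independent outcomes, each with one overall test at .05 and either allowed to win, the rate is 1 − 0.95² = 9.75%. For correlated outcomes I simulated 200,000 trials per correlation with no effect in any arm and 20 per arm:

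| Correlation | Both required, overall test | Either, overall test | Either, 4 unadjusted tests against placebo | Either, all 6 unadjusted pairwise tests |
|---|---|---|---|---|
| 0 | 0.26% | 9.7% | 17.4% | 23.0% |
| 0.3 | 0.43% | 9.5% | 16.9% | 22.5% |
| 0.5 | 0.85% | 9.2% | 16.1% | 21.4% |
| 0.7 | 1.56% | 8.6% | 15.0% | 19.8% |
| 0.9 | 2.81% | 7.2% | 12.7% | 16.8% |

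The both-required column is for no effect on either outcome. If one outcome has a real effect and the other has none, a false joint claim still needs the null outcome to reach .05, so the rate cannot exceed 5%.

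**3. What the three arms add.** With one overall test per outcome they add nothing: a single outcome gives 5%. With three unadjusted pairwise tests, a single outcome gives about 12%.

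**4. Checking candidate rules.**
- *Fixed order, overall tests only.* The second outcome is tested at .05 only if the first is significant. The family-wise rate is at most 5%.
- *Fixed order, with pairwise contrasts at .05 after each significant overall test.* This is closed within one outcome but not across two. Suppose one arm truly differs on fasting insulin, the other two are equal, and 1-hour insulin has no effect. Once the fasting test is passed, one true-null fasting contrast and the 1-hour overall test each get a full .05. If they are independent, that gives 1 − 0.95² = 9.75%. Simulation (20,000 trials per setting, difference of 1.0 to 3.0 SD) gave 9.2-10.2% at correlation 0, 8.5-9.1% at 0.5 and 7.0-8.2% at 0.9. This rule does not secure 5%.
- *.025 per outcome, with the overall test gating the pairwise tests.* Each outcome is closed at .025, so the total is at most 0.025 + 0.025 = 5%.

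**5. Power cost of .025 per outcome at 60 completers.** Power falls from 73% to 62% with no covariate gain, or from 80% to 71% at a covariate correlation of 0.385. With no covariate gain, 80% power needs 84 completers (84/0.8 = 105 enrolled), against 70 at .05 (70/0.8 = 87.5, so 88 enrolled).

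**The case against.** A reader might infer that the false-positive rate is well above 5%. The documents do not support that. Inflation requires a rule that either outcome may win, and the protocol states none; a requirement that both succeed is an equally possible reading and keeps the rate at or below 5%.

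The larger figures have a second weakness. "Using an analysis of covariance" with one f for three groups reads most naturally as a single overall test, and the only t-tests named are within-arm. Unadjusted pairwise tests between arms are neither planned nor excluded. The four-tests-against-placebo column is weaker still: at 1 year the placebo arm has already been on active treatment, so an intact placebo contrast no longer exists. All of this stands.

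It can also be said that success rules often sit in a separate analysis plan, which may exist here, and that this is a pilot. Both points limit how serious the issue is. They do not remove it, because the protocol has its own section headed as the statistical analysis plan, covering power, missing data and tests. It commits there to an 80% power claim and a .05 test without a rule that gives the .05 a meaning for two primary outcomes.

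**Conclusion.** The point holds as a failure to fix the error rate, not as proof of a given inflation. The rate is at most 5%, about 7-10%, or up to about 23%, depending on which unstated rule is applied. The 7-10% case lies closest to the sample-size text, which implies one overall test per outcome, but it still needs the either-outcome rule. The ranges rest on normal outcomes, 20 per arm and an assumed correlation of 0 to 0.9. The power cost rests on f = .38 and on a covariate correlation that the protocol does not give. This is worth correcting before unblinding; it does not invalidate the design.

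**What to change.** Before unblinding, state a fixed order for the two outcomes, for example fasting insulin first, as listed, with 1-hour insulin tested only if fasting is significant. Limit the confirmatory claim to one overall three-group test per outcome at .05, of the same type as the planned between-group comparison, and label pairwise contrasts as supportive. This takes a sentence or two and costs no alpha on the first outcome.

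The downside is that 1-hour insulin cannot be claimed confirmatorily if fasting insulin fails. The listing order is not a stated hierarchy, and the sponsor should choose knowing that the Power Calculations and Assumptions report a larger preliminary effect on 1-hour insulin (50%) than on fasting insulin (25-40%).

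If pairwise claims on both outcomes are wanted, use .025 per outcome with the overall test gating the pairwise tests, and accept the power loss or enlarge the trial.

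Under either option, define the 1-year comparison so that it is consistent with the reassignment of placebo patients at 6 months. As written, those passages must be reconciled before any contrast can be called primary.
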